#### Switch to controlled mechanical ventilation

In both groups, switch to protective controlled ventilation will be indicated if patient develops at least one of the following conditions: PSV support > 20 cmH_2_O; PEEP ≥ 15 cmH_2_O; unstable hemodynamic status (SBP < 90 mmHg with vasoactive drug); active cardiac ischemia (dynamic ST changes on cardiac monitor or electrocardiogram); unstable arrhythmias; uncontrolled hypertension (SBP > 180 mmHg); abrupt decrease in the level of consciousness (RASS <− 3); dangerous agitation (RASS > + 2); pH < 7.30; PaO_2_/FiO_2_ ratio ≤ 100 mmHg; necessity to perform diagnostic test (e.g., computed tomography (CT scan) or bronchoscopy).

Controlled ventilation will be set on volume mode with Vt 6–8 mL/kg PBW, RR to control pH, unchanged PEEP and FiO_2_. Controlled ventilation will be thereafter adjusted according to clinical evolution. Patients switched to controlled ventilation will be reassessed at least every 8 h and they will be switched back to PSV or PSV + sigh (to maintain study group assignment) targeting the aforementioned settings and adjustments as soon as all the following conditions are met: patient is able to trigger ventilator breaths; PaO_2_/FiO_2_ > 100 mmHg; PEEP < 15 cmH_2_O; pH ≥ 7.3; stable hemodynamic status with stable or decreasing doses of vasopressors for ≥ 6 h.

#### Rescue therapies

In the case of desaturation (SpO_2_ ≤ 90%) it will be crucial to exclude hemodynamic impairment as a possible cause. Also, airway obstruction and ventilator malfunction must be ruled out. Provided those factors are excluded, a rescue step-up strategy will be allowed: institution of protective controlled mechanical ventilation (see above for settings) and performance of recruitment maneuvers at 40–50 cmH_2_O, PEEP ≥ 15 cmH_2_O, prone positioning and inhaled nitric oxide, extracorporeal membrane oxygenation. Patients undergoing controlled ventilation and rescue treatments will be reassessed at least every 8 h and switched back to PSV or PSV + sigh (to maintain study group assignment) with the aforementioned settings and adjustments as soon as all the following conditions are met: patient can trigger ventilator breaths; PaO_2_/FiO_2_ > 100 mmHg; PEEP < 15 cmH_2_O; pH ≥ 7.3 and stable hemodynamic status with stable or decreasing doses of vasopressors for ≥ 6 h.

### Weaning protocol and criteria for reintubation

#### SBT

Patients with SpO_2_ ≥ 90% on FiO_2_ ≤ 0.4 and PEEP ≤ 5 cmH_2_O, no agitation, hemodynamically stable with norepinephrine ≤ 0.1 μg/kg/min or equivalent and at a stable or decreasing dose for 6 h [19] and without any of the aforementioned criteria for switch to controlled ventilation will undergo the SBT. For patients in the PSV group, the attending physician will perform the SBT directly. For patients in the PSV + sigh group, the attending physician will first withdraw sigh, wait 60 min and confirm the criteria: if confirmed, the SBT will be performed; if not, sigh will be reintroduced and the clinical criteria will be checked again to repeat the procedure after at least 8 h.

The SBT will last at least 60 min with a combination of PEEP 0–5 cm H_2_O and PSV 0–5 cm H_2_O. At the end of the 60 min, the patient will fail the SBT if any of the following are present: criteria to start the SBT not confirmed; sustained (> 5 min) respiratory rate > 35 bpm; heart rate > 140 bpm; SBP > 180 or < 80 mmHg; marked complaint of dyspnea; increased somnolence with elevated PaCO_2_ and/or pH < 7.3; active cardiac ischemia (dynamic ST changes on cardiac monitor or electrocardiogram); abrupt decrease in the level of consciousness with RASS <− 3 or if cough is not strong enough to clear secretions.

Patients who fail the SBT will be switched back to PSV or PSV + sigh (to maintain study group assignment) and clinical criteria will be checked again to repeat the procedure after at least 6 h.

Patients who pass the SBT will be extubated or, in the presence of tracheostomy, mechanical ventilation will be discontinued. If a patient is reintubated or mechanically ventilated through a tracheostomy again within 48 h, PSV or PSV + sigh (to maintain study group assignment) will be restored. If a patient remains extubated or separated from the ventilator for > 48 h data collection only will continue.

#### Reasons for reintubation

After elective extubation, reintubation should be promptly performed if at least one of the following criteria is present: cardiac arrest; respiratory arrest (respiratory pauses with loss of consciousness or gasping for air); respiratory failure with SpO_2_ < 90% and/or RR > 35 bpm despite non-invasive ventilation; decreased level of consciousness impairing ability to protect airway; hemoptysis or hematemesis impairing ability to protect airway; abundant secretions that cannot be effectively cleared or are associated with lobar collapse, acidosis, hypoxemia or change in mental status; surgical/invasive procedure requiring sedation/anesthesia +/− neuromuscular blockade such that patient is no longer be able to sustain unassisted breathing or hemodynamic instability with SBP < 80 mmHg despite vasoactive drugs.

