### Standard of care

In all patients, standard of care for intubated patients with hypoxemic acute respiratory failure (e.g., restrictive fluid strategy, early appropriate antibiotics, prophylaxis of gastric stress ulcer and deep vein thrombosis, semi-recumbent positioning, respiratory physiotherapy, adequate nutrition, monitoring of sedation, pain and delirium, tracheostomy and non-invasive ventilation for post-extubation respiratory failure) will be granted throughout the whole ICU stay in accordance to local protocols.

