### Study endpoints

#### Primary endpoint

The primary endpoint will be to verify the clinical feasibility of PSV + sigh vs. PSV. Feasibility will be assessed by comparing the number of patients in each group experiencing at least one of the following failure criteria [20]: switch to controlled ventilation following presence of one of the aforementioned reasons for ≥ 24 h consecutively; use of PEEP ≥ 15 cmH_2_O, prone positioning, inhaled nitric oxide, extracorporeal membrane oxygenation or reintubation within 48 h from extubation following one of the aforementioned reasons.

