### Data collection

At enrollment, before the sigh test we will anonymously collect patients’ demographic information (e.g., age, sex, height, weight), past (e.g., hypertension, chronic medications) and recent (e.g., etiology of the acute respiratory failure, days since intubation) medical history, severity of lung injury (e.g., ventilation setting, arterial blood gases, respiratory system compliance, diagnosis of acute respiratory distress syndrome (ARDS)) and of systemic involvement (e.g., presence of shock, number of organ failures) and finally, ventilation data (e.g., RR, Vt, PEEP, FiO_2_, PSV level).

In both groups, for the first 24 h, we will assess the SpO_2_/FiO_2_ ratio, RR and PSV tidal volume every 4 h to further characterize physiologic response to sigh over time.

From day 1 (i.e., within 24 h from randomization) to day 28 or death or discharge from the ICU, the following data will be collected every day between 6:00 and 10:00 in the morning: arterial SpO_2_, arterial and central venous blood gas analyses, ventilation settings and pattern (i.e., sigh pressure level, sigh tidal volume, PSV level, PSV tidal volume, respiratory rate, PEEP, FiO_2_, minute ventilation, P0.1, mean airway pressure), heart rate, arterial blood pressure, central venous pressure, cumulative fluid balance, patient’s comfort assessed using a visual analog scale (VAS), RASS value, SOFA score and dosage of sedative agents and vaso-active drugs.

Moreover, each day we will collect information on use of rescue treatments (i.e., recruitment manoeuvers, use of PEEP ≥ 15 cmH_2_O, prone positioning, inhaled nitric oxide, extracorporeal membrane oxygenation), tracheostomy, switch from the allocated treatment to the other study arm for ≥ 24 h, switch to controlled ventilation for ≥ 24 h, reason for switch to controlled ventilation, adverse events (i.e., hemodynamic instability with hypotension with SBP < 90 mmHg despite vasoactive drugs; arrhythmias; radiographic evidence of barotrauma with pneumothorax, pneumomediastinum, pneumatocoele, or subcutaneous emphysema), SBT performance and reason for SBT failure, extubation or separation from mechanical ventilation, reintubation and reason for reintubation with time. We will collect data on day 28 for all enrolled patients on mortality, extubation that occurred outside the ICU and readmission to ICU.

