### Statistical analysis

Continuous normally distributed variables will be expressed by their mean and standard deviation or as medians and their interquartile ranges when not normally distributed. Categorical variables will be expressed as number and proportion (%). To assess the feasibility of PSV + sigh as compared to PSV (i.e., the primary endpoint), we will compute the proportion of patients experiencing at least one of the following events in each arm: switch to controlled ventilation for ≥ 24 h consecutively; use of PEEP ≥ 15 cmH2O, prone positioning, inhaled nitric oxide, extracorporeal membrane oxygenation or reintubation within 48 h from extubation.

We will compare the two proportions using the one-tailed non-inferiority test for proportions with a 5% tolerance. We will use 0.05 as the significance level. The same method will be adopted to evaluate the safety of PSV + sigh, which is a secondary endpoint. Prevalence of sigh responders in the two arms will be compared using the chi-squared or Fisher’s exact test. Ventilator-free days will be calculated as the difference between the duration of follow up (up to 28 days) and the number of days of intubation before successful extubation or separation from mechanical ventilation for tracheostomized patients. For all the secondary endpoints, we will use the chi-squared or Fisher’s exact test in the case of binary variables or the *t* test or Wilcoxon signed rank test for continuous variables. Time to death or extubation will be analyzed using Kaplan-Meier survival curves. Adjustement for potential confounding factors will be evaluated using appropriated regression models.

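### Under the Primary endpoint section, a patient reintubated within 48 h for isolated respiratory failure without prior NIV is not a failure; under the Statistical analysis section the same patient is

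*Protocol article*

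**What the plan says.** All references are to the Protocol article.

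- **Primary endpoint:** the reintubation component is "reintubation within 48 h from extubation following one of the aforementioned reasons".
- **Reasons for reintubation:** this is the only list of such reasons. Its item for respiratory failure as such reads "respiratory failure with SpO_2_ < 90% and/or RR > 35 bpm despite non-invasive ventilation". The other items are cardiac or respiratory arrest, reduced consciousness, bleeding, secretions, a procedure under sedation or anaesthesia, and haemodynamic instability. One of them also names hypoxaemia, but only alongside secretions: "abundant secretions that cannot be effectively cleared or are associated with lobar collapse, acidosis, hypoxemia or change in mental status".
- **Statistical analysis:** the proportion to be computed for the primary comparison ends with "extracorporeal membrane oxygenation or reintubation within 48 h from extubation". No reason is required. The abstract's Methods paragraph and the objective at the end of the Background also require none.
- **Standard of care:** usual care for all patients includes "tracheostomy and non-invasive ventilation for post-extubation respiratory failure", and this "will be granted throughout the whole ICU stay in accordance to local protocols".
- **Data collection:** the daily record includes "reintubation and reason for reintubation with time". The list in the article does not name NIV.
- **Randomization:** blinding is not feasible. The Discussion answers the risk of bias by saying that the protocol regulates every process that can influence the primary outcome.

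**The concern.** The endpoint is meant to capture failure to remain on assisted ventilation or free of the ventilator. Early reintubation for plain respiratory failure is a central example. Under the Primary endpoint section, whether it counts turns on something else: whether NIV was tried first. Local protocols govern that step and unblinded staff carry it out, so the Discussion's assurance does not fully reach it.

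The direction matters because the primary test is for non-inferiority. If the sigh arm truly has more of these reintubations, leaving some out shrinks the excess and makes non-inferiority easier to claim. If NIV before reintubation is used differently in the two arms, the counted difference moves even when the true reintubation rates are equal.

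**Working it through.** **1. The text, for one patient.** Take a patient electively extubated and then reintubated within 48 h for SpO2 below 90% or a respiratory rate above 35. NIV was not tried, and no other listed reason or failure component applies.

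| Section | Listed reason required? | Scored as failure? |
|---|---|---|
| Primary endpoint | Yes | No |
| Statistical analysis | No | Yes |
| Abstract, Methods | No | Yes |
| Background, objective | No | Yes |

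Another component need not catch this patient. The SBT section returns a patient reintubated within 48 h to the assigned assisted mode, so 24 h of controlled ventilation does not follow automatically.

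**2. The plan's own sample size.** Inputs from Sample size and Statistical analysis: failure 22% (PSV) and 15% (PSV + sigh), tolerance 5 points (read as absolute), one-sided alpha 0.05, power 0.80.

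n = [0.22×0.78 + 0.15×0.85] × (1.645 + 0.842)² / (0.05 + 0.07)² = 128.4, so 129 per arm. This matches the plan; power at 129 is 80.2%. The sample size is not in dispute.

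**3. Effect on the error rate.** The document gives no reintubation or NIV rates, so every rate below is an assumption. True failure is placed at the margin, 22% vs 27%, where a correct test claims non-inferiority 5% of the time. Let r be the respiratory reintubation rate in an arm and s the share of those uncounted. The counted rate is p = true rate − s×r. Then

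SE = √{[pC(1−pC) + pS(1−pS)]/129}

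P(claim non-inferiority) = Φ[(0.05 + pC − pS)/SE − 1.645]

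where C is PSV and S is PSV + sigh.

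| Assumed r, PSV / sigh | Uncounted, PSV / sigh | Counted, PSV vs sigh | SE | (0.05 + pC − pS)/SE | False non-inferiority |
|---|---|---|---|---|---|
| any | none | 22.0% vs 27.0% | 0.0535 | 0 | 5.0% |
| 8% / 8% | 30% / 30% | 19.6% vs 24.6% | 0.0516 | 0 | 5.0% |
| 6% / 8% | 30% / 30% | 20.2% vs 24.6% | 0.0518 | 0.116 | 6.3% |
| 6% / 8% | 50% / 50% | 19.0% vs 23.0% | 0.0507 | 0.197 | 7.4% |
| 6% / 11% | 30% / 30% | 20.2% vs 23.7% | 0.0515 | 0.291 | 8.8% |
| 6% / 11% | 50% / 50% | 19.0% vs 21.5% | 0.0500 | 0.500 | 12.6% |
| 6% / 11% | 60% / 60% | 18.4% vs 20.4% | 0.0492 | 0.610 | 15.0% |
| 8% / 8% | 0% / 20% | 22.0% vs 25.4% | 0.0529 | 0.302 | 9.0% |
| 8% / 8% | 20% / 0% | 20.4% vs 27.0% | 0.0528 | −0.303 | 2.6% |

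In the 6% / 8% rows, 2 of the 5 excess points are respiratory reintubations. In the 6% / 11% rows all 5 are. The last two rows show a 20-point difference in NIV use between arms, a shift of 0.20 × 8% = 1.6 points, in each direction.

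**4. Effect on power at the design rates.** If 5%, 10% or 20% of all failures went uncounted in both arms, power at 129 per arm would be 79.5%, 78.8% or 77.6%.

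**The case against.** A reader might infer that such a patient will be scored as a success in the primary analysis. The document does not support that as a fact. The Statistical analysis section, which says what will be computed, has no reason condition, and under it the gap disappears. That stands, and it is why the point is framed as a conflict between sections. It does not settle the matter. The Primary endpoint section is the dedicated definition, and the Statistical analysis section also drops the reason condition from the controlled-ventilation component, so it may only be an abbreviated restatement.

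It is also tempting to say that no other listed reason could cover a hypoxaemic patient. Some will qualify through secretions, respiratory arrest, reduced consciousness or haemodynamic instability, none of which requires NIV. Others will fail through controlled ventilation for at least 24 h or a rescue treatment. The gap is limited to isolated hypoxaemia or tachypnoea with direct reintubation.

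NIV is named as standard care for all patients, so trying it first is the expected course, and nothing in the document supports a bypass share of 30–60%. At 10% bypass, with the whole excess respiratory (6% vs 11%), the counted rates are 21.4% vs 25.9% and the false non-inferiority rate is about 6%. A difference in NIV use between arms could also run the other way and make the test conservative.

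Finally, the article does not show that NIV goes unrecorded, because the eCRF is not shown. The reason for reintubation is collected, so a count of all reintubations within 48 h can be derived. A count conditional on NIV needs NIV itself to be known.

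**Conclusion.** The concern holds in this limited form. Followed as written, the Primary endpoint section leaves out reintubation within 48 h for isolated respiratory failure without prior NIV, unless another listed reason or component applies. Three other places in the article count it. Local NIV protocols and unblinded staff mean that the scoring can differ by centre or arm.

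The size cannot be fixed from the document. At the 22% vs 27% boundary the false non-inferiority rate is unchanged at 5% when equal rates lose equal shares. It is about 6–7% if 2 of the 5 excess points are respiratory and 30–50% go uncounted. It reaches about 9–15% only if the whole excess is respiratory, 30–60% go uncounted and nothing else captures these patients. A 20-point difference in NIV use on an 8% reintubation rate gives about 9% or about 2.6%, depending on direction. The upper figures are bounds under stacked assumptions and not expectations. The correction is worth making because these events are true extubation failures and the cost is very small.

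**What to change.** Reconcile the Primary endpoint section with the Statistical analysis section, the abstract and the Background objective on which reintubations count. State, for endpoint counting only, that a reintubation within 48 h for respiratory failure (SpO2 below 90% and/or respiratory rate above 35) counts whether or not NIV was tried first. If any version conditional on NIV is kept, record prior NIV (yes/no) beside the reintubation reason.

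The bedside criteria under Reasons for reintubation are unchanged, and no view is taken on when to use NIV or when to reintubate.

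The cost is one sentence, aligned wording in the other sections and, if needed, one eCRF field. The observed failure rate may be slightly higher. The change does not remove every influence of local NIV practice, since a patient in whom NIV averts reintubation is not a failure under either wording. It removes only the dependence of the count on NIV once reintubation has happened.

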### Standard of care

In all patients, standard of care for intubated patients with hypoxemic acute respiratory failure (e.g., restrictive fluid strategy, early appropriate antibiotics, prophylaxis of gastric stress ulcer and deep vein thrombosis, semi-recumbent positioning, respiratory physiotherapy, adequate nutrition, monitoring of sedation, pain and delirium, tracheostomy and non-invasive ventilation for post-extubation respiratory failure) will be granted throughout the whole ICU stay in accordance to local protocols.

### End of follow up

Enrolled patients will be observed until day 28, ICU discharge or death, whichever comes first.

### Study endpoints

#### Primary endpoint

The primary endpoint will be to verify the clinical feasibility of PSV + sigh vs. PSV. Feasibility will be assessed by comparing the number of patients in each group experiencing at least one of the following failure criteria [20]: switch to controlled ventilation following presence of one of the aforementioned reasons for ≥ 24 h consecutively; use of PEEP ≥ 15 cmH_2_O, prone positioning, inhaled nitric oxide, extracorporeal membrane oxygenation or reintubation within 48 h from extubation following one of the aforementioned reasons.

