As prospective clinical trials including long-term use of sigh during assisted ventilation have not been performed yet, we conceived a pilot randomized controlled trial (RCT) to verify the clinical feasibility of the addition of sigh to PSV (PSV + sigh) in comparison to standard PSV. Therefore, the objective of the present trial is to determine whether ventilation by PSV + sigh can be applied early and safely in intubated patients with AHRF and successfully maintained until extubation. Specifically, the primary endpoint is to evaluate whether PSV + sigh, as compared to PSV, is associated with reduced failure of assisted ventilation, with failure defined as (1) prolonged switch to controlled ventilation; (2) use of rescue therapies for refractory hypoxia or (3) early need for reintubation after elective extubation.

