### Sample size

The sample size was computed based on the hypothesis that PSV + sigh might decrease the rate of failure of assisted ventilation compared to standard PSV. Based on previous data [21], the expected proportion of failure in patients undergoing PSV will be 22% and we hypothesized a proportion of 15% for patients in the PSV + sigh group. Assuming non-inferiority of PSV + sigh treatment, with a tolerance of 5% we estimated that a sample size of 258 patients (with 129 patients per study arm) will be sufficient to assess feasibility of the PSV + sigh strategy in this pilot phase with power of 0.8 and alpha 0.05.

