## Discussion

PROTECTION is a pilot randomized controlled trial to test the long-term clinical feasibility of the addition of sigh to PSV in comparison to standard PSV. If positive, it will provide the basis for a future larger trial aimed at verifying the impact of PSV + sigh on a composite outcome endpoint including 28-day survival and ventilator-free days. Moreover, it will provide physicians a physiologically sound addition (i.e., sigh) to standard PSV for lung protection able to favor assisted ventilation.

Mortality remains considerably high (around 40%) in intubated patients with AHRF [6]. The clinical severity of lung injury at presentation and early appropriate treatment are the main determinants of patients’ outcomes [19]. However, while the lungs recover, VILI might significantly impact survival [1]. Recent studies testing strategies that enhance lung protection (e.g., early referral to an extracorporeal membrane oxygenation (ECMO) center [22]; use of muscle relaxants during the first 48 h after intubation [23]; early use of extended sessions of prone positioning [24]) yielded significantly decreased mortality. However, such trials enrolled only the most severely ill patients with AHRF on controlled mechanical ventilation. A recent large observational study [6], instead, showed that most ventilated patients admitted to the ICU have mild to moderate AHRF or ARDS that leads to considerably high mortality (≈ 35%) anyway. Moreover, the same study reported that around 30% of invasively ventilated patients with AHRF and ARDS are on some form of spontaneous breathing from day 1 after intubation, independent of the severity of their illness [6], and this proportion likely increases within 1 week. Thus, there is an urgent need for interventions that increase lung protection during assisted ventilation.

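### The primary failure list omits death and cannot see sigh being stopped, so a patient who dies on the ventilator without a listed event counts as a feasibility success

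*Protocol article*

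**What the plan says.** The Background of the protocol article sets the objective: whether PSV + sigh "can be applied early and safely in intubated patients with AHRF and successfully maintained until extubation". It then narrows the primary endpoint to failure of assisted ventilation.

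Under Primary endpoint, "Feasibility will be assessed by comparing the number of patients in each group experiencing at least one of the following failure criteria". The criteria are a switch to controlled ventilation lasting at least 24 consecutive hours, PEEP of 15 cmH2O or more, prone positioning, inhaled nitric oxide, extracorporeal membrane oxygenation, or reintubation within 48 h of extubation. Statistical analysis repeats the same events: "we will compute the proportion of patients experiencing at least one of the following events in each arm". The two proportions are compared with a one-tailed non-inferiority test, 5% tolerance, significance level 0.05.

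Death appears elsewhere. It ends the allocated ventilation (Adjusting ventilation settings) and observation (End of follow up), and 28-day mortality is a secondary endpoint. Data collection records each day a "switch from the allocated treatment to the other study arm" lasting at least 24 h, but no endpoint or analysis in the article uses that record.

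**The concern.** The list is closed and is given twice in the same terms, so it is a fixed rule and not a detail left open. Under that rule two kinds of patient count as successes although PSV + sigh was not maintained until extubation:

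- a patient who dies on assisted ventilation, or within 24 h of a switch to controlled ventilation, with no listed rescue;
- a sigh patient who is moved to plain PSV and stays there.

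The first matters most. Death can remove a patient before a listed failure occurs. If that happens more often under sigh, the sigh arm's failure proportion falls because of deaths, and the one-sided test moves towards declaring non-inferiority. The second means that the primary result alone cannot show whether sigh was in fact sustained, which is what the objective asks.

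**Working it through.** **Inputs.** From Sample size: failure 22% under PSV and 15% under PSV + sigh, tolerance 5 points, power 0.8, alpha 0.05, 129 per arm. From Statistical analysis: one-tailed test. The documents give no rate of death without a listed event and no rate of stopping sigh, so every such rate below is an assumption.

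**The plan's own figure.** n per arm = (1.645 + 0.842)² × (0.22×0.78 + 0.15×0.85) / (0.05 + 0.07)² = 128.4, rounded up to 129. The stated size reproduces.

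**Chance of declaring non-inferiority.** With pC and pT the failure rates in the PSV and sigh arms as counted:

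P(NI) = Φ[(0.05 − (pT − pC)) / SE − 1.645], SE = √[(pC(1−pC) + pT(1−pT)) / 129].

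Example at 22% vs 22%: SE = 0.0516, so Φ(0.05/0.0516 − 1.645) = Φ(−0.675) = 0.25. In the first two tables P(NI) comes from exact binomial enumeration of the unpooled test, which agrees closely with the formula.

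**Deaths that hide failures.** Let the true sigh rate, as it would be seen if death did not come first, lie at the margin: 27% vs 22%.

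| Hidden by death | PSV as counted | Sigh as counted | P(NI) = false-positive rate |
|---|---|---|---|
| none | 22% | 27% | 0.051 |
| 2 points, sigh only | 22% | 25% | 0.104 |
| 5 points, sigh only | 22% | 22% | 0.253 |
| 5 points, both arms | 17% | 22% | 0.052 |
| same fraction (5/27) in both arms | 17.9% | 22% | 0.075 |

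Two points are 0.02 × 129 = 2.6, about 3 patients. The inflation comes from imbalance: equal losses leave the error rate where it was. At the planning rates, loss in the PSV arm only (17% vs 15%) works against the claim, and P(NI) falls from 0.805 to 0.457.

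**Stopping sigh.** Suppose half the sigh arm reverts to the PSV rate of 22%.

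| True rates, PSV vs sigh | Sigh as counted | P(NI) without stopping | P(NI) with half stopped |
|---|---|---|---|
| 22% vs 27% (sigh worse) | 24.5% | 0.051 | 0.123 |
| 22% vs 15% (planning rates) | 18.5% | 0.805 | 0.527 |

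Dilution helps the claim only in the first row.

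**Counting event-free death as failure** (formula, rates added to 22% and 15%):

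| Event-free deaths, PSV / sigh | Rates compared | P(NI) at 129 per arm | n per arm for power 0.80 |
|---|---|---|---|
| 5% / 5% | 27% vs 20% | 0.74 | 154 |
| 10% / 10% | 32% vs 25% | 0.69 | 174 |
| 15% / 15% | 37% vs 30% | 0.66 | 191 |
| 5% / 15% | 27% vs 30% | 0.10 | not relevant |

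In all four rows the endpoint as written gives 0.80. In the last row it would usually declare non-inferiority despite 10 points more event-free deaths under sigh.

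**The case against.** A reader might infer that both omissions favour the non-inferiority claim whatever happens. The documents do not support that. Nothing in them suggests that event-free deaths would fall in one arm only; equal losses do no harm to the error rate, and at the planning rates stopping sigh makes the claim harder to reach.

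A reader might also take the Discussion's statement, "Mortality remains considerably high (around 40%) in intubated patients with AHRF", as the size of the problem. It is all-cause mortality in a broader population. This trial excludes moribund patients, those with PaO2/FiO2 of 100 mmHg or less and those with cardiovascular instability. Many deteriorating patients would also meet a criterion for switching to controlled ventilation and so could register a listed event before dying. What remains is death on assisted ventilation or within 24 h of a switch, and its frequency cannot be derived.

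Deaths are not hidden either: 28-day mortality is compared between arms and time to death or extubation is plotted. That stands, but a secondary comparison does not alter how the primary result is read.

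Finally, it is tempting to require a per-protocol analysis. Analysis sets are commonly left to a SAP, and excluding switched patients removes precisely those in whom sigh was not maintained. As an assumed example, take a true sigh rate of 27%, with 20% of the arm switched and failing at 40%. The rest fail at (0.27 − 0.20×0.40)/0.80 = 23.75%, and P(NI) is 0.15 per protocol against 0.05 as randomised. The objection to that remedy is right. Stopping sigh also has no counterpart in the PSV arm, so it does not belong in the between-arm composite.

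**Conclusion.** The point holds in a limited form. The failure list, as fixed in two sections, classifies a patient who dies before separation without a listed event as a success, and it does not register loss of sigh. Both conflict with an aim of safe use maintained until extubation.

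The death omission biases towards non-inferiority only if event-free deaths hide more failures under sigh than under PSV. On the assumption that 2 to 5 points are hidden in the sigh arm alone, with the true rate at the margin, the false-positive rate rises from 5% to 10–25%. Whether any such imbalance will occur cannot be judged from the documents. For loss of sigh, the issue is less the error rate than that the primary result does not answer whether sigh was kept up. The sample size is correct on its own inputs. This should be put right, but it does not invalidate the design.

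**What to change.** Keep the composite and the sample size. Fix in writing, before outcomes are analysed by arm:

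1. A supporting non-inferiority analysis, with the same test and 5-point tolerance, in which death by day 28 before a separation from the ventilator lasting more than 48 h counts as failure in both arms. State that the feasibility conclusion will be read together with it.
2. A separate feasibility measure: the share of PSV + sigh patients kept on sigh until SBT or extubation, with a 95% CI, derived from the daily sigh settings and the record of arm switches of at least 24 h. The planned withdrawal of sigh just before an SBT should not count as stopping.

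No per-protocol requirement is needed. Data collection already provides day-28 mortality for all enrolled patients, extubation and separation, arm switches and sigh settings, so the cost is wording and analysis time. The downside is power: with 129 per arm and the planning rates, the death-inclusive analysis has about 0.74 with 5% and 0.69 with 10% event-free deaths per arm (assumed), against 0.80 for the composite. The claim becomes somewhat harder to support.
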